13.7 Reporting of patients included in the medical file

The inclusion of the patient in the study will be marked by a pastille pasted on the cover page of her clinical file. . If the patient is included and randomized a second label will be placed on the medical record to indicate that she is taking either an antibiotic or a placebo.

13.8 Patient follow-up

The follow-up of all PCR + / PCR- patients will be recorded under the responsibility of the investigator by the clinical research technician.

In order to check for possible confounding factors, data concerning the management, the evolution of pregnancy, delivery and the characteristics at birth of the newborn will be collected.

Maternal follow-up will be carried out until the maternity leave.

The follow-up of premature newborns will be carried out until a corrected age of 36 weeks.

The follow-up of the newborns will be realized until the exit of the maternity.

Data on pregnancy outcome after inclusion in the study will be collected.

Data regarding vaginal sampling between 35 and 37 weeks will be collected.

Data concerning the prescription of antibiotics during pregnancy will be collected.

Data on delivery and neonatal follow-up before leaving the maternity ward will be collected.

13.9 Data collection

The data will be collected as the study progresses directly on the computer in the electronic CRF using the "cleanweb" software.

The data will be collected directly by the clinical research technician as the patient is delivered.

16.1 Number of subjects needed

We estimated the risk of preterm delivery to be 17% in the case of positive amniotic fluid PCR for Ureaplasma spp. or Mycoplasma hominis, (average assumption between 10 to 24% corresponding to published figures). In order to be able to show a reduction in the risk of preterm delivery by 50%, it is necessary to include 238 women in each group (α = 0.05, 1-ß = 0.80).

The prevalences published in the second trimester of positive PCR for Ureaplasma spp. and Mycoplasma hominis vary little according to studies and countries (USA or Switzerland) and are at least 15% by combining the two bacteria 26. The inclusion of 3200 patients who benefit from amniocentesis will achieve the desired number of patients.

16.2 Duration of the study and feasibility

The number of amniocentesis performed over one year in all centers participating in the study is approximately 3750 amniocentesis per year, distributed as follows:

- CHI of Créteil: 400

- Port Royal: 500

- Saint Vincent de Paul: 550

- CHI of Poissy 650

- Rothschild Keychain: 200

- Saint Anthony: 650

- Necker: 200

- Robert Debré: 600

Assuming an inclusion rate in the study of 40% (refusal of patients, twin pregnancies, malformations ...), the number of 3200 patients could be reached in 30 months on all centers that have agreed to participate in the study. study. The follow-up of patients and newborns is 6 months after the date of inclusion. The total duration of the study would be 36 months. The number of patients lost to follow-up should in principle be very low because they are pregnant patients who receive very regular follow-up and for whom the delivery will necessarily take place in a maternity ward.

16.3 Data Analysis

The data capture will be carried out as and when under the responsibility of the investigator through the software "cleanweb". The computer file will be processed under STATA (College Station, TX, USA)

Data analysis will be done in INSERM unit U149 by [name] and [name].

The study will distinguish 3 groups of patients according to the studied factor and the prescription of an antibiotic treatment: with a negative PCR, with a positive PCR without antibiotic treatment, with a positive PCR with antibiotic treatment.

These groups will be compared to each other for

• Clinical criteria collected at baseline: maternal age and level of education, obstetrical history, gestational age at baseline.

• Criteria collected during pregnancy: number of consultations, treatment, concomitant treatments, protocol outputs, adverse events and unblinding.

Then, an intention to treat the existence of an "antibiotic" effect in the form of a difference, in the case of a positive PCR, between the "placebo" group and the "josamycin" group for the main endpoint and the criteria of secondary judgments.

Comparisons will use non-parametric statistical tests whenever staffing or distribution constraints require it. For categorical variables, the chi2 test and the Fisher test will be used. Variance analysis and Kruskal and Wallis nonparametric testing will be used for continuous variables.

The effects will be measured as relative risk, with their 95% confidence interval.

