12.1 Primary judgment criterion

Occurrence of premature delivery between 22 and 37 weeks

12.2 Secondary judgment criteria.

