3.5 Randomization and Treatment Administration

The randomization will be done according to a stratified randomisation list on the centers, prepared by the URC Henri Mondor.

The randomization will be done directly online from the cleanweb software.

The batch of treatment will then be given to the patient by the pharmacy, on a specific order of the investigator (Josamycin or placebo, at a dosage of 1 gram morning and evening orally for 10 days).

A blind survey card will be given to patients. (See chapter on the lifting of blindness)

The treatment batches will be distributed in the pharmacies of the investigative centers by the AGEPS. They will be labeled in accordance with the legislation in force for drugs intended for therapeutic trials. In order to guarantee blindness, josamycin or placebo treatment batches will look identical

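### Randomisation is stratified by centre, but section 16.3 names only unstratified tests for the primary endpoint: a minor mismatch that makes the analysis slightly conservative

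*Protocol*

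**What the plan says.** **Design.** Protocol section 3.5: "The randomization will be done according to a stratified randomisation list on the centers". No block size is given.

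**Endpoint.** Section 12.1 defines a binary primary criterion: "Occurrence of premature delivery between 22 and 37 weeks".

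**Analysis.** Section 16.3 plans an intention-to-treat comparison of josamycin with placebo among PCR-positive women, for the main and secondary criteria. On the test it says "For categorical variables, the chi2 test and the Fisher test will be used"; on the effect measure, "The effects will be measured as relative risk, with their 95% confidence interval". It names no stratified test, centre term or adjusted model. It does not say whether the relative risk is crude or stratified.

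**Sample size.** Section 16.1: "We estimated the risk of preterm delivery to be 17% in the case of positive amniotic fluid PCR", described as "average assumption between 10 to 24% corresponding to published figures". It asks for 238 women per group to detect a halving of that risk with alpha 0.05 and power 0.80.

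**The concern.** Stratifying the list by centre, with balance inside each centre, keeps differences between centres out of the treatment contrast. An unstratified chi-squared test computes its standard error as if those differences could still contribute. If centre risks differ, that standard error is somewhat too large, the true type I error falls below the nominal 5%, and the confidence interval is a little too wide.

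The protocol is not silent here: it names the tests for the primary comparison, and they do not follow the randomisation it describes. The question is whether the mismatch matters for validity, power or sample size.

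**Working it through.** **1. The protocol's own figure.** Inputs from 16.1: 17% against 8.5%, alpha 0.05 (taken as two-sided), power 0.80. The unpooled two-proportion formula is

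n = (1.960 + 0.842)² × [p₁(1 − p₁) + p₂(1 − p₂)] / (p₁ − p₂)²
= 7.849 × (0.17 × 0.83 + 0.085 × 0.915) / 0.085² = 7.849 × 0.2189 / 0.007225 = 237.8, i.e. 238 per group.

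This is the protocol's figure. The pooled version gives 241. The sample size is sound on its own terms.

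**2. Expected direction and size.** With exact balance within centre, the unstratified variance under the null is too large by the share of outcome variance lying between centres. Call this share ρ = Var(centre risks) / [0.17 × 0.83]. The unstratified z statistic then has standard deviation √(1 − ρ), and

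true type I error ≈ 2 × [1 − Φ(1.960 / √(1 − ρ))].

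- ρ = 0.0136: 1.960 / 0.9932 = 1.973, giving 4.8%.
- ρ = 0.0326: 1.960 / 0.9836 = 1.993, giving 4.6%.
- ρ = 0.041: 1.960 / 0.9793 = 2.001, giving 4.5%.

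**3. Simulation.** There were 200,000 trials per scenario, with 478 women (476 rounded to even centre sizes) over the eight centres listed in section 16.2 in proportion to their volumes, and exact 1:1 balance within centre. (The protocol's section on type of study says seven centres; the eight listed volumes serve only as weights.) The between-centre spread is assumed, with risks rescaled to average 17%. Neither test uses a continuity correction. CMH is the Cochran-Mantel-Haenszel test stratified by centre.

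| Assumed centre risks (before rescaling) | ρ | Type I error, chi-squared / CMH | Power at relative risk 0.5, chi-squared / CMH |
|---|---|---|---|
| No spread | 0 | 5.05% / 4.95% | 80.6% / 80.2% |
| 12-22%, evenly spread | 0.0072 | 5.05% / 5.04% | 80.6% / 80.4% |
| 10-24%, evenly spread | 0.0136 | 4.83% / 4.90% | 80.8% / 80.8% |
| 10-24%, centres at the two ends | 0.0326 | 4.67% / 4.94% | 80.9% / 81.3% |
| 5-35%, evenly spread | 0.041 | 4.73% / 5.09% | 81.1% / 81.6% |

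The simulation standard error is about √(0.05 × 0.95 / 200,000) = 0.05 points for the type I error and √(0.8 × 0.2 / 200,000) = 0.09 points for power. The two values of 5.05% are therefore compatible with 5%.

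Further runs with 238 per group and other assumed spreads agree (chi-squared / CMH):

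- centre risks about 10-26%: type I error 4.8% / 5.0%;
- about 10-27%: 4.8% / 5.0%, power 80.5% / 80.6%;
- about 5-34%: type I error 4.6% / 5.0%;
- about 5-37%: 4.3% / 5.0%, power 80.9% / 82.0%.

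**4. Precision of the estimate.** In every row of the table the crude and Mantel-Haenszel log relative risks have the same sampling standard deviation to four decimals. Only the estimated standard error differs. Under the alternative it is 0.2606 crude against 0.2595 stratified at 10-24% evenly spread (ratio 0.996), and 0.2604 against 0.2572 at 5-35% (ratio 0.988). The interval on the log scale is thus about 0.4% to 1.2% wider than it need be.

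**The case against.** **An unstratified primary test after stratified randomisation is valid.** This stands. The error is on the safe side, and the unstratified chi-squared test reaches the planned 80% power in every scenario above. With little or no spread, the stratified test is 0.2 to 0.4 points lower in the table.

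**Wide spreads have no support in the documents.** This also stands. The only range given, 10% to 24%, comes from published studies and is not a spread between these centres. Section 7 restricts centres to those close to one laboratory. The wide scenarios are bounds.

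**The choice may be left to an SAP that is not shown.** This stands in part. The wording of 16.3 does not rule out a stratified relative risk, so calling the planned estimate crude is an inference from the tests named. But 16.3 does fix the tests, and they are unstratified. An SAP naming a stratified test would then differ from the protocol.

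**Stronger readings that the documents do not support:**

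- *That much of the precision gained by stratifying is lost.* Balance within centre already protects the estimate; only its estimated standard error is affected, by about 1% at the wide end.
- *That naming Fisher's test leaves the trial underpowered.* Fisher's power at 238 per group is about 76%, but this holds equally with no centre differences. It comes from discreteness and not from ignoring centre. Section 16.3 reserves alternative tests for cases where numbers or distributions demand them. With 238 × 0.17 ≈ 40 and 238 × 0.085 ≈ 20 expected events, the text does not clearly call for Fisher on the primary endpoint.
- *That adjusting for previous preterm delivery would add useful power.* That gain needs a prevalence and a risk ratio that the protocol does not give.

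**Conclusion.** The mismatch between sections 3.5 and 16.3 is real, and its consequence is small. If centre risks differ, the unstratified test and interval are slightly conservative:

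- at about 10-26%, a type I error of about 4.8% instead of 5.0%, with power essentially unchanged;
- at about 5% to 34-37%, about 4.3-4.6%, with about 0.5 to 1 point of power lost;
- with no spread, stratifying costs about 0.3 points of power.

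A positive result from the unstratified test would remain valid, and 238 per group needs no change. These figures rest on assumed between-centre spreads, exact balance within centre, and the eight listed volumes as weights. The direction is firm and the size is uncertain within that narrow range. Severity is minor: the reason to act is that the analysis should follow the randomisation and that doing so is free.

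**What to change.** Add one sentence to section 16.3: the primary intention-to-treat comparison of josamycin with placebo on preterm delivery uses the Mantel-Haenszel relative risk stratified by centre, with its 95% confidence interval, and the Cochran-Mantel-Haenszel test without continuity correction. Keep the unstratified chi-squared test as a supportive analysis. If an SAP already sets a stratified analysis, align 16.3 with it.

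The cost is that sentence. It needs no extra patients or data, since centre is already part of each patient's identifier (section 13.2), and both methods are standard commands in STATA, the package named in 16.3. The simulated centres included two with only 24 women each, and the stratified test kept its type I error between 4.9% and 5.1%, so small centres are no obstacle.
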